### Statistical analysis

In descriptive analysis of data, central tendency and dispersion indices (mean, median and standard deviation) will be used. Kolmogorov–Smirnov test will be used to test whether two random samples are drawn from the same normal distribution. Otherwise its nonparametric equivalent will be used. Depending on the circumstances, paired t-test and analysis of covariance will be used to compare pre- and post-rehabilitation program. Other analytical tests will be used as required during the data processing phase. SPSS software (V20.0, IBM Corporation, New York, USA) will be used for statistical data analysis and the significance level for all tests will be 0.05.

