μ1: mean of the studied variable in the first group

μ2: mean of the studied variable in the second group

α=0.05

β=80%

Z= 1.96

Based on previous studies, a power of 85% and level of significance of 95% was determined for this study. We obtained a sample size of 15 individuals for each group (total = 30), which takes into consideration a 20% drop out.

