### Study design

The study will not involve complications for participants, but if there is extreme difficulty with cooperation for participants the test will be discontinued. All participants were informed both orally and in writing about the study process. Written consent to participant were obtained before the study start. There is no criteria for intervention modification in this study protocol. To improve adherence to intervention protocols, every training session the examiner provide feedback to all participants and inform them about the training progress. The rehabilitation sessions and duration are flexible for participant.

We randomly assigned participants in 1:1 ratio, intervention and control group. The intervention group undergo the rehabilitation training program.

The two groups were matched for age and gender. Those in the control group do not receive any rehabilitation programs during the study. The randomization was applied by random number table (those assigned an odd number, control group; those assigned an even number, intervention group).

***Study procedures***. Pre-rehabilitation, the SNR (50%) of all participants was measured using the word in noise (WIN) test. In addition, a binaural TFS test and the SSQ questionnaire score of all participants are evaluated (see section
*Outcomes* below).

***Rehabilitation training***. Participants identify the set of 16 consonants using one-interval forced-choice procedure and feedback with correct answer. On each test the participants select one of the stimuli from the set of 16 syllables. The participants are informed while the stimulus is presented that they should identify its middle consonant. Following each stimulus presentation, a 4 × 4 visual display of the response alternatives appear on a computer monitor and the participant select the response by using the computer mouse.

Each participant select a box, if they click the box correctly, the box turn green and if they choose the wrong answer, the box turn red. The participant is given visual feedback by showing the correct VCV with a yellow box. No time limit is be imposed on the participant's responses. Each experimental run consists of 64 trials derived from a different random-order presentation of the 64 syllables in the stimulus set. Each run is last 16 to 30 min depending on the participant's response time. The total duration of rehabilitation sessions are e five weeks. Experiments are controlled by a desktop PC.

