### Speech stimulus process

The TFS speech consists of single syllable recorded in / a / C / a / with various 16 consonant format which included Aja, Aka, Ara,…. and it is pronounced by a native-speaking man. The analogue signals are converted to digital a 16-bit at 44.1 KHz sampling frequency. The stimulus synthesis process is performed in MATLAB software and the software is provided in C programming language.

The original bandpass is filtered into 16 bands of equal bandwidth on a log frequency scale spanning 80 to 8020 Hz. Each Bandpass signal is decomposed to ENV and TFS by Hilbert transform. The ENV component is discarded and TFS component is normalized and TFS component in each band summed lastly creating TFS speech.

After rehabilitation, the SNR (50%) using the WIN test, and a binaural TFS test and SSQ questionnaire will be evaluated again in intervention group. Results will be compared in intervention and control groups before and after the rehabilitation program.

***Outcomes***.
*SNR (50%):* single syllable words in the presence of noise at different signal-to-noise ratios (0, + 4, + 8, + 12, + 16, + 20, + 24) as binaural in two study groups and compare the SNR (50%). Differences in scores before and after rehabilitation training between the two groups will be compared.

The Words-in-Noise (WIN) materials were developed to evaluate the ability of listeners to understand words in multitalker babble. The WIN involves in which the level of the noise is fixed and five words are presented at seven signal-to-noise ratios from 24 to 0 dB in 4 dB decrements. The 35 words are spoken by a native male speaker. The metric of interest is the signal-to-noise ratio (S/N) at which recognition performance is 50%, which is a value determined with the Spearman Karber equation see (
*Extended data:* S2).

Binaural TFS test: determines the binaural change of phase difference at different frequencies in intervention and control groups before and after rehabilitation training.

The correlation between the results of speech perception test scores in the presence of noise with the results of binaural TFS test in the two groups after rehabilitation program will be assessed.

*SSQ questionnaire score:* provided to each group before and after rehabilitation training. Scores between intervention and control groups will be compared (
*Extended data:* S3).

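### The Kolmogorov–Smirnov pre-test is worded as a test that two samples are the same, not that data are normal, so the choice of analysis can depend on the training effect

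*Protocol article*

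**What the plan says.** The Statistical analysis section of the protocol article sets out a two-step rule. The first step is "Kolmogorov–Smirnov test will be used to test whether two random samples are drawn from the same normal distribution". The second is "Otherwise its nonparametric equivalent will be used". The parametric methods come next: "Depending on the circumstances, paired t-test and analysis of covariance will be used to compare pre- and post-rehabilitation program". The section also states that "the significance level for all tests will be 0.05", which by its wording covers the pre-test too.

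The section does not name the two samples. It does not say that normality is checked within each group, on differences or on residuals. It does not name the nonparametric method.

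The comparison that matters is between groups. Under Outcomes, for the SNR (50%) measure: "Differences in scores before and after rehabilitation training between the two groups will be compared".

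**The concern.** Two groups can each be exactly normal and still not come from the same normal distribution: it is enough that their means differ. A rule that requires one common distribution before the parametric method may be used is therefore failed by a difference in means, and a difference in means is what the trial hopes to find.

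If the rule is applied to outcome data after training, the test that yields the final p-value is chosen by a statistic that responds to the treatment effect. At stake are whether the analysis is fixed in advance, and whether the result is reported as a baseline-adjusted difference in dB or only as a rank comparison.

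**Working it through.** **Inputs from the protocol article**
- Sample size: "We obtained a sample size of 15 individuals for each group (total = 30), which takes into consideration a 20% drop out".
- Power: "a power of 85% and level of significance of 95% was determined for this study". The list above that sentence also gives 80% against β, so both power values are carried.
- Two-sided 0.05 (Z = 1.96) and 1:1 allocation.
- No means or SDs are given, so the sample size cannot be reproduced forwards. The dropout step is consistent: 12 / (1 − 0.20) = 15.

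**Shift implied by the stated design.** With equal SDs the article's formula becomes n = 2(z₁₋α/₂ + z₁₋β)² / d², so d = √(2/n) × (z₁₋α/₂ + z₁₋β).
- n = 12, 85% power: √(2/12) × (1.960 + 1.036) = 1.22
- n = 12, 80% power: √(2/12) × (1.960 + 0.842) = 1.14
- n = 15, 85% power: √(2/15) × 2.996 = 1.09
- n = 15, 80% power: √(2/15) × 2.802 = 1.02

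These values are inferred. A smaller shift of 0.8 SD is shown as an assumption.

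**How often normal data fail the rule as written.** Two independent normal groups with equal SD, differing only in mean; two-sample Kolmogorov–Smirnov test at 0.05; 4,000 simulated trials per cell (Monte Carlo standard error at 64%: √(0.64 × 0.36 / 4000) = 0.8 percentage points).

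| Shift (SD) | n = 12 per group | n = 15 per group |
|---|---|---|
| 0 | 3.1% | 2.7% |
| 0.5 | 13% | 14% |
| 0.8 | 30% | 35% |
| 1.02 | 47% | 55% |
| 1.09 | 54% | 63% |
| 1.22 | 64% | 72% |

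Repeat simulations gave 63–64% and 71–72% in the last row.

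If the two samples are instead pre and post scores in one group (n = 15, assumed correlation 0.7, 3,000 trials), the failure rate is 0.1% at no shift, 7% at 0.5 SD, 53% at 1.0 SD and 77% at 1.22 SD.

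**Contrast with a real normality check.** A Lilliefors test on within-group residuals (15 per group, 2,000 trials) rejected in 5.1%, 5.1% and 3.8% at shifts of 0, 1.1 and 2.0 SD. The dependence on the effect comes from the stated definition, not from pre-testing for normality as such.

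**What the switch does to the conclusion**
- t-test, replaced by Mann–Whitney when the pre-test rejects: at n = 12 and 1.22 SD, power 82.1% against 81.9% for the t-test throughout. Type I error 5.6% (n = 12) and 5.2% (n = 15).
- ANCOVA, replaced by an unadjusted Mann–Whitney test on post scores (n = 12, 1.22 SD): power 89.5% against 89.4% at an assumed pre–post correlation of 0.5, and 96.8% against 97.3% at 0.7. Type I error was 5.5% and 6.3%; a further run gave 5.9–6.3%, against about 5% for ANCOVA alone.

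**If a one-sample normality check was meant.** At 12–15 values, the uncorrected test with estimated mean and SD detects lognormal data (log-SD 0.5) in 0.4–0.7% of samples and exponential data in 0.5–1.6%. With the Lilliefors correction the figures are 19–27% and 35–46%.

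**The case against.** The strongest reply is that the sentence is a badly worded normality check. The word normal and the parametric/nonparametric fork both point that way, and rewording would cure the literal fault. This is probably right about intent. It does not make the written rule correct, and the check probably intended is weak at this sample size even with the Lilliefors correction.

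The samples are also unnamed. If only the two groups at baseline were compared, the training effect could not influence the rule. This stands, and it limits the point to post-training scores, change scores or pre-versus-post comparisons.

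Naming the fallback test and the diagnostics may properly be left to a statistical analysis plan that is not shown. That also stands: their absence is not the fault. The fault is the definition that is given.

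Some stronger readings are tempting but unsupported:
- **A real effect always triggers the switch.** It is a probability, about a third of trials at 0.8 SD and about two thirds at 1.22 SD.
- **The trial would lose much power.** Taken alone, an unadjusted rank test is weaker than ANCOVA: at 0.8 SD and an assumed correlation of 0.7 with n = 12, 42% on post scores and 65% on change scores, against 73%. But the rule switches mainly when the result is already significant either way, so in the two-step simulations power hardly moves.
- **Baseline adjustment is certainly lost.** The article does not say so, and rank methods that adjust for baseline exist. The loss is possible because the fallback is unnamed.
- **A normality check would have almost no power.** That holds for the uncorrected version only.

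**Conclusion.** The point holds in a limited form. As written, the rule tests sameness rather than normality. Applied to outcome data after training, it would send normal data to the nonparametric route in about 30–35% of trials at an assumed 0.8 SD, and in 63–72% at the inferred 1.22 SD.

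The numerical harm is small: power changes by at most about one percentage point, and type I error reaches about 6% if the fallback is an unadjusted rank test on post scores. What matters is that the method, and possibly the estimand, would depend on the effect under study.

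The figures rest on normal data with equal SDs, on the rule being applied literally to post-training or change scores, and on a shift the article does not state. The two-step ANCOVA results also rest on assumed pre–post correlations of 0.5 and 0.7.

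**What to change.** Delete the two sentences that set up the pre-test. State that the between-group analysis is ANCOVA of the post-training score on group with the baseline score as covariate, whatever any preliminary test shows. Check its within-group residuals graphically. Fix one baseline-adjusted sensitivity analysis in advance, for example a permutation test of the ANCOVA group coefficient; rank ANCOVA is an acceptable alternative.

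ANCOVA is already named and baseline scores are taken in all participants, so the cost is a few sentences and one short extra analysis. It does need end-of-study scores in the controls. The Outcomes text implies that these are collected, but the Discussion says final testing is done only in the intervention group, and those passages must be reconciled.

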### Participants

Participants were recruited from elderly people, aged between 60 and 75 years old, referred to the audiology clinics of Iran University of Medical Sciences and were informed by phone about the study. They were selected based on previous clinical examination, including otoscopy, tympanometry and pure tone audiometry test (PTA) to identify type and level of a hearing loss. In a preliminary interview, speech perception difficulty was evaluated with a question if they had difficulty in understanding speech in noise. Those who respond yes were entered into the study. Later to define difficulty in understanding speech in noise we adapted questionnaire which was used by Tokgoz-Yilmaz
*et al*.
^25^.

We performed Mini Mental State Examination (MMSE) questionnaire in order to rule out prominent cognition difficulty in participants.

Participants were informed that can withdraw from the study at any time. Privacy concerning information and results of participants are respected.

The schematic diagram of study procedures is shown below
*Extended data:* Figure S1.

***Inclusion and exclusion criteria***.
*Inclusion criteria:* individuals with mild to moderate hearing loss and aged between 60–75 years, having diploma or higher degree; right-handedness (assessed using Edinburgh handedness inventory); speaking native language and being monolingual; complaint about speech in noise perception difficulties and normal condition of middle ear function.

*Exclusion criteria:* those who do not meet the inclusion criteria, unwillingness for participation in each step of study, conductive hearing loss and abnormal middle ear, central nervous system disease, head trauma, history of seizure attack and epilepsy, and use of psychiatric and nervous system drugs. Individuals with obvious cognitive problems, as diagnosed by Mini Mental State Examination (MMSE), were also excluded.

***Sample size***. The following formula is used to determine the number of samples in each group with the concern that the two groups are independent and dependent variables in this study are quantitative.
$$\text{n}=\frac{{\left(Z_{1-\frac{\text{α}}{2}}+Z_{1-\text{β}}\right)}^{2}({\sigma_{1}}^{2}+{\sigma_{2}}^{2})}{{\left({\text{μ}}_{1}-{\text{μ}}_{2}\right)}^{2}}$$

α1: standard deviation of the studied variable in the first group (case, exposed, or intervened)

α2: standard deviation of the studied variable in the second group (control, unexposed, or compared)

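### No named test is tied to the randomised comparison, and the paired t-test that the plan lists does not test it

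*Protocol article*

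**What the plan says.** The analysis of effect is set out in the Statistical analysis section: "Depending on the circumstances, paired t-test and analysis of covariance will be used to compare pre- and post-rehabilitation program". The sentence before it provides for a switch after a distribution check, "Otherwise its nonparametric equivalent will be used", and the sentence after it leaves room for more: "Other analytical tests will be used as required during the data processing phase". None of the three says which test carries the comparison of intervention with control.

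Other sections point to a between-group question:

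- Study design: "We randomly assigned participants in 1:1 ratio, intervention and control group", with an untreated comparator: "Those in the control group do not receive any rehabilitation programs during the study".
- Sample size (under Participants): the formula is for two means, on the ground that "the two groups are independent and dependent variables in this study are quantitative".
- Outcomes (under Speech stimulus process), for SNR (50%): "Differences in scores before and after rehabilitation training between the two groups will be compared". The same section also says that questionnaire scores will be compared between the groups.

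On end-of-study measurement, the section Speech stimulus process says: "After rehabilitation, the SNR (50%) using the WIN test, and a binaural TFS test and SSQ questionnaire will be evaluated again in intervention group". The Discussion repeats that the closing tests are done in the intervention population only.

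**The concern.** A pre/post paired t-test in one arm asks whether that arm's mean changed. Change can come from training, from familiarity with the word lists or the phase task, from regression to the mean, or from altered self-rating on a repeated questionnaire. Only the control arm separates training from the rest, and the paired test leaves the control arm out. Running a paired test in each arm and finding one significant and the other not is no substitute, because it does not test the difference between the arms.

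The plan lists a test that can answer the question (ANCOVA with a group term) beside one that cannot. It gives both a pre-versus-post target and no rule for which applies. Anyone following the text could report that training works when the two groups do not differ.

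**Working it through.** **1. The plan's own figure.** The article states 15 per group, allowing for 20% dropout, from n = (z₁₋α/₂ + z₁₋β)²(σ₁² + σ₂²)/(μ₁ − μ₂)². No means or SDs are given, so 15 cannot be reproduced. With equal SDs the formula can be inverted for the standardised difference, d = √[2(z₁₋α/₂ + z₁₋β)²/n], with 15 × 0.8 = 12 left after dropout:

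- 85% power: √[2(1.96 + 1.036)²/12] = 1.22; with all 15 analysed, 1.09.
- 80% power: √[2(1.96 + 0.842)²/12] = 1.14; with all 15 analysed, 1.02.

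Both power values are shown because the parameter list and the text beneath it differ. In every case d is a difference between two independent groups, so the trial was sized for a contrast that a paired test does not address.

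**2. The paired test when training does nothing.** Assumptions, none of them in the documents: both arms gain the same g (in SDs of the score), the pre-post correlation r is 0.5 or 0.7, and scores are normal. The test is two-sided at 0.05.

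- Standardised change: dz = g/√[2(1 − r)]. At r = 0.5, dz = g. At r = 0.7, dz = g/0.775, so g = 0.5 gives 0.645.
- Rejection probability p: noncentral t with n − 1 degrees of freedom and noncentrality dz√n.
- Probability of 'intervention significant, control not': p(1 − p), since the arms are independent.

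Example: n = 15, r = 0.5, g = 0.5. Noncentrality is 0.5 × √15 = 1.94, p = 0.438, and p(1 − p) = 0.438 × 0.562 = 0.246.

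| Shared gain g | r | p, n = 12 | p, n = 15 | p(1 − p), n = 12 | p(1 − p), n = 15 |
|---|---|---|---|---|---|
| 0 | either | 0.050 | 0.050 | 0.048 | 0.048 |
| 0.2 | 0.5 | 0.097 | 0.112 | 0.088 | 0.099 |
| 0.2 | 0.7 | 0.130 | 0.154 | 0.113 | 0.130 |
| 0.3 | 0.5 | 0.158 | 0.192 | 0.133 | 0.155 |
| 0.3 | 0.7 | 0.232 | 0.287 | 0.178 | 0.205 |
| 0.5 | 0.5 | 0.353 | 0.438 | 0.228 | 0.246 |
| 0.5 | 0.7 | 0.532 | 0.643 | 0.249 | 0.230 |

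**3. ANCOVA under the same conditions.** In a simulation of 5,000 trials per setting, the group effect from an ANCOVA of post score on group and baseline was significant in 4.7% to 5.6% of trials, whatever the shared gain. The simulated paired-test rates agreed with the table to within sampling error.

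**4. Both tests available.** With no shared gain at all, counting the trial positive if either the intervention-arm paired test or the ANCOVA is significant gave about 9% (8.5% to 9.4%) in place of 5%.

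**The case against.** Four points can be made for the plan.

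*The between-group contrast is stated.* This stands. A reader might infer that the protocol has replaced the randomised comparison with a pre/post one. The Outcomes text does not support that, since it says differences will be compared between the groups. The fault is narrower: that comparison is linked to no named test, and the sentence that names tests has a different target.

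*The text joins the two tests with 'and'.* This also stands. A reader might infer a declared choice of one test or the other after seeing the results. The sentence can equally mean paired tests for within-arm change and ANCOVA for the arm comparison, and its opening condition may refer back to the distribution check. But it does not say so, and the sentence on other tests does tie further choices to the data-processing stage.

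*The size depends on an assumed retest gain.* Correct. It is tempting to quote about one in four for the 'significant in one arm only' pattern. That is the ceiling, because p(1 − p) cannot exceed 0.25. It is reached near a 0.5 SD gain, and with no gain the figure is about 0.05. The range has to be shown.

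*A condensed article may leave the model to a fuller document.* This holds for covariates, analysis set and model details. It does not cover a stated pre/post target that does not match the stated question.

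A reader might also infer that, because closing tests are described for the intervention arm only, the paired test is the only analysis possible. The documents do not settle this: the same section promises a between-group comparison of pre/post differences, which needs control post-scores. It is a contradiction to be reconciled.

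**Conclusion.** The point holds in this form: the article intends a comparison of two randomised groups, attaches no named test to it, and lists a paired t-test that cannot make it. With no training effect, the intervention-arm paired test would be significant in about 10–15%, 16–29% and 35–64% of trials for shared gains of 0.2, 0.3 and 0.5 SD. The pattern of significance in the intervention arm alone would arise with probability about 0.09–0.13, 0.13–0.20 and 0.23–0.25 (simulation put the upper end at 0.3 SD slightly higher, at 0.21). ANCOVA holds about 5%. These figures rest on assumed gains, correlations of 0.5 to 0.7 and 12 to 15 per arm. That the paired test ignores the control arm needs no assumption. The wording should be changed before the data are analysed.

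**What to change.** Replace the sentence on the paired t-test and ANCOVA with wording such as: *The effect of training on each outcome is the difference between groups, with 95% CI, from an analysis of covariance of the end-of-study score on group and the participant's own baseline score, with participants analysed in the group to which they were randomised. Changes within each group are reported descriptively, without tests. Any other analysis is labelled exploratory.* The opening conditional phrase goes.

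Add age and gender as covariates only if they were used in the allocation. Study design says the groups were matched on them but describes only odd and even random numbers, so this has to be established first.

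A between-group t-test of change scores would also test the right contrast, but ANCOVA is more precise. Relative to the variance of a single score, the variance factor is 1 − r² for ANCOVA and 2(1 − r) for change scores: 0.75 against 1.00 at r = 0.5, and 0.51 against 0.60 at r = 0.7 (assumed correlations).

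Cost: one paragraph of text. ANCOVA is already listed and baselines are taken in all participants. The fix depends on control post-scores, so the statements in Speech stimulus process and the Discussion that closing tests are for the intervention group only must be reconciled with the between-group comparison under Outcomes. If controls were not going to be retested, that adds one assessment for up to 15 people.

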### Objectives

The main aim of the study is to evaluate the impact of special rehabilitation training based on TFS on improvement of speech in noise perception in an elderly population with mild to moderate hearing loss.

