### Terminology used in this study

*Mild to moderate hearing loss:* auditory thresholds ≤25dB within the frequency<2000 Hz and 25–70 dB HL with frequency 2000–8000 Hz.

*TFS-LF test:* software designed by Hopkins and Moore in 2010. The test is originally based on measuring the interaural phase differences
^15^.

*Interaural phase difference (IPL):* lowest difference in the phase of the wave in each ear and dependent frequency sound waves and difference in time between ears
^15^.

*Signal to noise ratio (SNR):* ratio of the power of a signal (meaningful information) to the power of background noise (unwanted signal), expressed in decibels (dB). Larger numbers for signal characteristics mean better and more useful than unwanted noise information
^23^. In this study the signal-to-noise ratio levels were 0, 4, 8, 12, 16, 20, and 24 dB.

*Speech in noise score:* measured by Persian version of WIN test (PARWIN list), which is expressed as a percentage by performing a single syllable word test. The PARWIN test is a version of the Richard H. Wilson WIN test, in which the background noise in this test is baffled noise
^24^. PARWIN test is used to estimate SNR (50%) using Spearman Karber equation.

*Speech, Spatial and Qualities of Hearing Scale (SSQ) questionnaire:* used in previous studies in elderly individuals with communication disorders caused by hearing loss. From the original version of the SSQ questionnaire, its validity and reliability native version were confirmed (validity, 96% reliability) and included 47 items in three subgroups of speech perception, spatial hearing, and auditory quality. Based on the results of the questionnaire, the mean score of each item and item of each index will be measured for the research participants.

*Rehabilitation training:* auditory rehabilitation was based on TFS. The intervention group will be asked to identify vowel consonant vowel words (VCVs) that have only TFS preserved and their envelope discarded. It is based on that VCVs that processing and converting to TFS speech. In this process the ENV of VCVs are eliminated and only TFS will be kept.

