listener have difficulty to perform the test with chosen frequency. This limitation led to develop TFS-AF test. In TFS-AF test IPD is fixed for example is 180 degree with frequency adaptively varied to determine a threshold. In this study, we used TFS-LF test in all participants because TFS-LF test provides a good measure of sensitivity to binaural TFS. The aim of this study was to improve speech in noise perception with fast transition consonant vowel words (VCV) and identify interaural phase difference (IPD) which TFS-LF is more appropriate. TFS-LF were performed in three frequencies, 250, 500 and 750 Hz
^15^. 

Signal-To-Noise Ratio (SNR) 50% is used routinely by audiology clinics. Age related hearing loss have decline speech discrimination ability in similar SNR compare to normal hearing ability and require higher SNR
^23^.

Several test and questionnaire are performed to assess the ability to hear and process sounds and speech from different locations which called spatial hearing speech. In this study we use The Speech, Spatial and Qualities of Hearing Scale (SSQ).

The validity of TFS-LF, SNR 50% and SSQ questionnaire to recognise hearing loss have been confirmed previously
^15,
22,
23^.

We designed stimulus software which divided sound signal to envelope (ENV) and TFS. In this program ENV is removed and only TFS is preserved.

In conclusion in this study, we will attempt to prove by special rehabilitation training based on TFS damage age-related hearing loss can be improved.

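### All tests are judged at 0.05 and no outcome is designated primary, so the false-positive risk over three or more efficacy outcomes exceeds 5%

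*Protocol article*

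**What the plan says.** The Statistical analysis section sets one threshold: "the significance level for all tests will be 0.05". It mentions no order among outcomes and leaves room for further tests to be chosen during data processing.

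The Outcomes part, under Speech stimulus process, lists three instruments: SNR (50%) from the words-in-noise test, the binaural TFS test and the SSQ score. A between-group comparison is stated for SNR (50%) and for SSQ. The TFS test is to be determined in both groups before and after training, and a general sentence just before the list has results compared between the groups. A correlation between speech-in-noise and TFS results is added. The Discussion again names the three instruments together as the means of judging the training. Nowhere is one called primary or secondary.

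Two of the instruments yield several scores. The Discussion says "TFS-LF were performed in three frequencies, 250, 500 and 750 Hz". The Terminology section gives the SSQ three subgroups and 47 items, and says that "the mean score of each item and item of each index will be measured for the research participants".

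The nearest thing to a priority is the aim in Objectives, the impact of "special rehabilitation training based on TFS on improvement of speech in noise perception in an elderly population". The Sample size text does not help: its formula refers only to the "mean of the studied variable in the first group" and the matching quantity in the second group.

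**The concern.** A 5% threshold limits the risk of a false positive conclusion to 5% only if the conclusion rests on one test. Here three instruments are offered as evidence of efficacy, each may be tested at 0.05, and the text does not say which one decides. The protocol frames the study as an attempt to prove that training helps, so the reader will want to know which result would count as proof.

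The practical risk is that SNR (50%) shows nothing while another measure reaches p < 0.05 and carries the claim. That measure could be the SSQ, which is self-rated. Controls receive no rehabilitation and are not told the details of the intervention, but trained participants know that they were trained, so expectation can move their ratings. It could also be a single TFS-LF frequency.

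**Working it through.** **1. The plan's own figure.** The Sample size text gives 15 per group at two-sided 0.05 (Z = 1.96), "which takes into consideration a 20% drop out". No mean difference or standard deviation is stated, so 15 cannot be reproduced, only back-solved. Twelve evaluable per group gives 12 / (1 − 0.20) = 15. With equal standard deviations the printed formula is n = 2(z₁₋α/₂ + z_power)² / d², where d is the standardised difference. Power appears both as 80% (printed as β) and in the statement that "a power of 85% and level of significance of 95% was determined for this study". With n = 12:

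- 80% power: d = √(2 × (1.960 + 0.842)² / 12) = 1.14
- 85% power: d = √(2 × (1.960 + 1.036)² / 12) = 1.22

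Neither value identifies the outcome for which the trial was sized.

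**2. Counting the tests.**

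- Firm count: one comparison for each instrument, so 3.
- Upper count, if TFS-LF is tested by frequency and SSQ by subscale: 1 + 3 + 3 = 7. The text describes these scores but does not state separate tests on them.

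**3. Chance of at least one false positive, no true effect, each test at 0.05.** For k independent tests it is 1 − 0.95ᵏ:

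- k = 3: 1 − 0.8574 = 14.3%
- k = 7: 1 − 0.6983 = 30.2%

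The documents give no correlations between outcomes. The table assumes a common correlation and uses 400,000 simulated sets of normal test statistics, rejecting when any exceeds 1.96 in absolute value.

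| Assumed correlation | 3 tests | 7 tests |
|---|---|---|
| 0 (exact) | 14.3% | 30.2% |
| 0.3 | 13.6% | 27% |
| 0.5 | 12.5% | 23% |
| 0.7 | 10.9% | 18% |
| 0.9 | 8.4% | 11% |

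Every entry exceeds 5%.

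**4. What each repair costs.** With a single primary test at 0.05, the error rate for the trial's conclusion returns to 5% and the sample size is unchanged. Keeping all outcomes co-equal under a Bonferroni split is dearer, taking 12 evaluable per group and the detectable differences in step 1 as the starting point:

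- Seven outcomes: 0.05 / 7 = 0.00714 per test. Power falls from 80% to 54%, or from 85% to 62%. Restoring it takes 20 or 19 evaluable per group. After 20% dropout that is 20 / 0.8 = 25, or 19 / 0.8 = 23.75, rounded up to 24.
- Three outcomes: 0.05 / 3 = 0.0167 per test. Holding power takes 17 or 16 evaluable per group. After dropout that is 17 / 0.8 = 21.25, rounded up to 22, or 16 / 0.8 = 20.

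The plan has 15 per group.

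**The case against.** The best defence has three parts.

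First, the stated aim is speech-in-noise perception, and SNR (50%) is listed first among the outcomes, so the intended primary may seem obvious. SNR (50%) is indeed the natural choice. But the aim names a construct, not an endpoint. The SSQ speech subgroup also fits it, and the Discussion brings interaural phase difference into the aim. The sentence in Outcomes that points to the 50% recognition level explains how the words-in-noise test is scored and does not rank the trial's outcomes.

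Second, this is a condensed article, and a statistical analysis plan, the registry entry or the SPIRIT checklist may say more. The method of multiplicity adjustment can fairly be left to such a document. The article is not silent, though: it fixes 0.05 for all tests, and a later adjustment would contradict that sentence.

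Third, the size of the problem is easily overstated. This stands, and it rules out three readings that a reader might infer:

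- *Any single p < 0.05 makes the trial positive by rule.* No success rule is written. The sentence sets a per-test level. The exposure comes from that level combined with the absence of a designated primary outcome.
- *At least seven endpoints will be tested.* Results by frequency and by subscale are described, but separate tests on them are not stated. Three is the firm count and seven is conditional.
- *The 47 SSQ items will each be tested.* Item means are to be measured, which is scoring. No item-level tests are planned, so a count of expected false positives among items has no basis in the text.

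**Conclusion.** The point holds in its limited form and should be corrected. The protocol applies 0.05 to every test, offers three instruments as efficacy outcomes, designates none as primary and ties its sample size to none. If a significant result on any of the three were taken as evidence that training works, the false-positive risk would be 14.3% under independence and 8.4% at an assumed correlation of 0.9, or about 2.9 to 1.7 times the nominal 5%. Seven tests would give 30.2%, falling to 11% at 0.9, but only if frequencies and subscales are tested separately. The figures rest on the count of tests, on no true effect for any outcome and, apart from the independent case, on assumed common correlations. The direction does not depend on these choices, because every case examined exceeds 5%.

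**What to change.** Before any outcome data are seen, state in the protocol:

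> The trial's conclusion rests on one test: the between-group comparison of post-training SNR (50%) by ANCOVA adjusted for baseline SNR (50%), at a two-sided level of 0.05. TFS-LF and SSQ are secondary and cannot establish efficacy on their own.

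Restrict the 0.05 sentence to this test. For the secondary outcomes, either Holm-adjusted p-values or estimates with confidence intervals and no confirmatory claim would do. State which SSQ and TFS-LF scores will be compared. In Sample size, name SNR (50%) as the variable and give the mean difference and standard deviation behind 15 per group.

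One contradiction must be settled first. Outcomes plans before-and-after comparisons between groups, but the text just above it has retesting in the intervention group, and the Discussion says that end-of-study tests are measured only in that group. Without post-training scores in controls the primary ANCOVA cannot be run, so these passages must be reconciled so that both groups are tested at the end.

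The cost is otherwise wording. ANCOVA is already among the planned methods and the sample size need not change. If control retesting was not in fact planned, it adds one more assessment for that group. The small downside is that TFS-LF or SSQ can no longer carry the conclusion alone.
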